**Figure 1. f1:**
[figure not shown]
Summary of study process.

**Figure 2. f2:**
[figure not shown]
Schedule of enrolment, interventions and assessments.

### Inclusion criteria

Patients will be included if they fulfil the following inclusion criteria: i) Sub-acute stroke in both men and women between the ages of 45 and 65 years; ii) Mini-Mental State Examination score ≥24; iii) Modified Rankin Scale ≤3; iv) patients with Brunnstrom stage for hand and leg ≥4; v) Modified Ashworth Scale ≤2; and vi) be able to comprehend and adhere to instructions.

### Exclusion criteria

The exclusion criteria will be as follows: i) Individuals who are experiencing balance problems as a result of neurological conditions other than stroke (for instance cerebellar impairment, inner ear dysfunction, or Parkinson’s disease); ii) individuals suffering from unstable angina, symptomatic heart failure, or uncontrolled hypertension; iii) acute stroke (flaccid stage); iv) physician determined unstable cardiovascular conditions; v) the patient has been diagnosed as having organ failure, including the heart, kidneys, and lungs; and iv) patients with any traumatic musculoskeletal injury to lower limbs.

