## Methods

### Protocol

The model consent form, data collection form and schedule of enrolment, interventions and assessments can be found as
*Extended data.*
^
24
^ This protocol adheres to the SPIRIT guidelines.
^
25
^

After gaining clearance from the Institutional Ethics Committee (IEC) of Datta Meghe Institute of Higher Education and Research (Deemed to be University), participants will be enrolled from the Physiotherapy Outpatient Department of Acharya Vinoba Bhave Rural Hospital Sawangi, Meghe, Wardha, Maharashtra. A total of 34 participants will be made aware of the study’s objectives and procedures and will be asked to sign written patient consent forms. All hemiplegic stroke patients who meet the inclusion and exclusion parameter will be included in the study. They will be further separated into Group A and Group B by means of simple random selection. Each group will consist of 17 people in total. The randomization procedure will be conducted using a computer-generated random number system. For sample distribution, we will use the sequentially numbered opaque sealed envelope technique. There will be no blinding procedure in this study. The principal investigator will generate allocation, enrol participants and assign participants to interventions. A departmental committee made up of the Post Graduate (PG), Guide, the Head of Department (HOD), the Principal of the Ravi Nair Physiotherapy College (RNPC) and a member of the Research Guidance Cell will oversee the project. Through routine treatment sessions, we will make sure that the patients follow the suggested treatment plan closely. If necessary, individuals will receive counselling or telephone reminders about their therapy appointments. Prior to and following the analysis, the outcome measures will be assessed. The study’s outcome indicators are as follows: The BBS, DGI, Trunk Impairment Scale (TIS), Functional Reach Test (FRT), 10 Meter Walk Test (10MWT) and Fall Efficacy Scale (FES) along with conventional treatment for balance and gait. mCIMT will be given in Group A in addition to conventional therapy, whereas Group B will receive the MRP in addition to conventional therapy.
Figure 1 and
Figure 2 depict the study design.

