### Statistical analysis

Samples taken in accordance with the protocol and recorded on a basis that includes all relevant characteristics. Dataset of outcome variables including demographic, physical, laboratory and vitals information will be collected and tabulated in Excel, and will be analysed using R-Software version 4.3. Demographic variables such as age and gender and physical examination (height, weight, BMI), laboratory parameters (haemoglobin, Erythrocyte Sedimentation Rate (ESR), Liver Function Test (LFT), Kidney Function Test (KFT)), and vitals (respiratory rate, pulse rate, systolic blood pressure, diastolic blood pressure and SpO
_2_ levels) will be collected. Outcome variables such as BBS, DGI, TIS, 10MWT, FRT and FES will be presented over descriptive statistics with categorical tabulation for frequency and percentage, while quantitative measurements with minimum, maximum, mean and standard deviation.

The primary outcome variables will include the BBS for measuring balance and the DGI for measuring gait outcome variables, the secondary outcome variables include the TIS, FRT, 10MWT and FES. Variables as primary and secondary parameters for their measuring assessment at different time visits will be assessed to find the significance in mean at 5% level of significance at P-value < 0.05. Statistical analysis will be performed for hypothesis testing for paired pre and post analysis using a paired t-test for normal data or non-parametric test such as Wilcoxon signed-rank test for non-normal data. Similarly, an unpaired t-test will be used for two independent groups for the change in parameters readings of primary and secondary variables at two different visits.

Data over the outcome variables will be analysed for normality (normal distribution) using Kolmogorov–Smirnov test. If data results over non normal distribution then alternate non parametric test will be used.

Confounding variables will be analysed with generalised linear model to find the random and fixed effects over the outcome variables. Association analysis for finding significance of cofounding parameters will be examined by using Chi-squared test or Fisher’s exact test or by using multi-variant analysis.

Full analysis set for the values of outcome variables will be analysed for the results missing data will be covered with imputation method by calculating the mean and median over the existing data.

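### Sub-acute stroke has no limits in time since onset, the acute-stroke exclusion is keyed to muscle tone, and the between-arm comparison is not adjusted for time since onset

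*Protocol article*

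**What the plan says.** Eligibility, in the Protocol article:

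- Inclusion criterion i is "Sub-acute stroke in both men and women between the ages of 45 and 65 years". It gives no lower or upper limit in days, weeks or months, and no such limit appears elsewhere in the text shown.
- Inclusion criteria iv and v are "patients with Brunnstrom stage for hand and leg ≥4" and "Modified Ashworth Scale ≤2".
- Exclusion criterion iii is "acute stroke (flaccid stage". This gloss is the only wording that marks off acute from sub-acute stroke.

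Allocation and analysis:

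- The 34 patients are divided "by means of simple random selection", 17 per group. No stratification is stated (Methods, Protocol).
- The variables to be collected are introduced with "Demographic variables such as age and gender and physical examination (height, weight, BMI), laboratory parameters" and continue with vital signs. Time since stroke is not named.
- For the arms, "an unpaired t-test will be used for two independent groups for the change in parameters readings", with a non-parametric alternative if the data are not normal.
- A separate paragraph says "Confounding variables will be analysed with generalised linear model to find the random and fixed effects over the outcome variables". It names no covariate.

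**The concern.** Sub-acute describes a phase after stroke and defines the population in all three objectives, yet the one discriminator given is a state of muscle tone. Someone applying or reading the criteria cannot tell how soon after onset a patient may enter, or how late. Two investigators could draw the line in different places and both comply.

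The statistical consequence follows from the outcome. The primary outcomes are six-week changes in BBS and DGI, and spontaneous change over six weeks plausibly depends on how long ago the stroke occurred. If entry times vary widely, that variation goes into the residual SD of an unadjusted comparison. With 17 per arm, the groups can also differ in time since onset by chance, and the named analysis does nothing about it.

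**Working it through.** **1. What the exclusion adds.** Inclusion i already requires sub-acute stroke, so an acute stroke fails before exclusion iii is reached. Inclusion iv requires Brunnstrom stage 4 or above in hand and leg. If the flaccid stage is the lowest Brunnstrom stage (the article does not define the stages), a flaccid patient fails there too. The Ashworth criterion is only an upper limit and would not exclude flaccid limbs by itself. Exclusion iii therefore removes nobody whom the inclusion criteria admit, and the undefined word in inclusion i does all the work.

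**2. The plan's own figures.** From Sample size calculation: difference 3.7, SD (4.7 + 3.5)/2 = 4.1, Z values 1.64 and 0.84.

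2 × (1.64 + 0.84)² × 4.1² / 3.7² = 15.1

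This matches the stated 15; adding 2 for dropout gives 17 per group. The point here does not depend on that calculation. It supplies only n = 17, 4.1 and 3.7.

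**3. Size of a chance imbalance.** For a baseline variable measured in SD units, the between-arm difference has standard error √(2/17) = 0.343.

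- Median absolute imbalance: 0.6745 × 0.343 = 0.23 SD.
- 95% limit: 1.96 × 0.343 = 0.67 SD.
- An imbalance of at least 0.5 SD occurs in about 14% of randomisations.

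**4. Effect on the BBS difference.** Shift = r × imbalance × SD of change. Two inputs are assumptions: r = 0.3 to 0.5 between (log) time since onset and six-week BBS change, which is not in the documents, and 4.1 used as the SD of change.

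| Imbalance | r = 0.3 | r = 0.5 |
|---|---|---|
| 0.23 SD (median) | 0.28 points (8% of 3.7) | 0.47 points (13%) |
| 0.67 SD (95% limit) | 0.83 points (22%) | 1.38 points (37%) |

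**5. Gain from adjustment.** The residual SD falls by 1 − √(1 − r²), which is 4.6% at r = 0.3 and 13.4% at r = 0.5. Before the cost of estimating the slope, that equals 1/(1 − r²) − 1 = 10% to 33% more patients. Estimating the slope multiplies the variance by about 1 + 1/(2 × 17 − 4) = 31/30 on average. The net variance ratio is 0.91 × 31/30 = 0.940 to 0.75 × 31/30 = 0.775, so the standard error falls by 3% to 12%, worth 6% to 29% more patients. Adjustment breaks even where r² = 1/31, that is r = 0.18.

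**6. Sensitivity to the SD.** The 4.1 averages a pre and a post SD and is not an SD of change. With an assumed pre-post correlation of 0.7, the SD of change is √(4.7² + 3.5² − 2 × 0.7 × 4.7 × 3.5) = 3.4. The shifts in step 4 then shrink by the ratio 3.4/4.1 = 0.83. The percentages in step 5 do not depend on the SD.

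The article gives no planning figures for DGI, so no size is computed for it.

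**The case against.** The strongest defence is that inclusion i positively requires sub-acute stroke. A reader might infer that the criteria admit any non-flaccid stroke, including one a few days old or one long past. The text does not support that, because such a patient must still pass inclusion i. A redundant exclusion admits no one. What stands is narrower: the phase is undefined, and the one gloss offered points to tone instead of time.

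Recovery stage should also not be confused with time. The Brunnstrom, Ashworth and Rankin criteria do bound motor and functional state; only time since onset has no number.

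A reader might further infer that onset date goes unrecorded, or that the blood tests and vital signs are the chosen confounders. Neither follows. The list of variables is illustrative, the data collection form is not shown, and the article does not assign those variables to the generalised linear model. That model could include time since onset. Choice of covariates is often left to an analysis plan, and an undefined window taken alone is close to missing detail. Still, the between-arm test that the article does name is unadjusted, and no correction is fixed.

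Finally, chance imbalance under randomisation is already reflected in the t-test's standard error. That is correct: type I error is not inflated, and the upper row of sizes, not the 95%-limit row, shows a typical trial. One person generates the allocation, enrols and assigns, which might suggest imbalance beyond chance. Nothing computed here relies on that.

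**Conclusion.** The point holds as a matter of definition and precision, not of bias. The entry phase is left to judgement with no stated upper limit, the tone-based exclusion does not help, and the named between-arm comparison ignores a variable that the investigator needs in order to apply inclusion i.

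Under the stated assumptions, a typical chance imbalance moves the BBS difference by about 0.3 to 0.5 points against a planned 3.7. An imbalance at the 95% limit moves it by 0.8 to 1.4 points. Adjustment would lower the residual SD by about 5% to 13%. These sizes rest on an assumed correlation of 0.3 to 0.5 and on 4.1 as the SD of change. With a weaker correlation the gain shrinks, and it disappears near 0.18. The point does not invalidate the trial, but it should be settled before recruitment, and Study status says that the study has not begun.

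**What to change.** - Record the date of stroke onset at screening, if the form does not already ask for it.
- Make the between-arm analysis of BBS and DGI change a linear model with treatment arm and (log) time since onset as prespecified fixed covariates, in place of the unadjusted t-test.
- Replace the tone-based gloss in exclusion iii with lower and upper limits in time since onset, and reconcile them with inclusion i. The limits are a clinical choice for the investigators. The Discussion describes the earlier motor relearning trial only as one in sub-acute patients and gives no limits that could be taken over.

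The cost is one degree of freedom, one form field and possibly a few patients turned away by a stated window. The eligibility wording needs a formal amendment. The Protocol amendments section says that further changes could not be made, so that statement has to be revisited. Recording the onset date and naming the covariate do not change who is eligible.

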### Interventions

*Criteria for discontinuing allocated interventions for a given trial participant*

If any patients in any of the allocated groups develop any complication (
*e.g.*, deep venous thrombosis), their participation will be discontinued in the study. The patients will then receive appropriate care and offered outpatient rehabilitation as needed. Study participants will be retained in the trial (unless they withdraw their consent) to enable follow-up data collection and to prevent missing data.

*Adherence and concomitant care*

During the first consultation, the importance of following the study guidelines and adhering to the allocated group will be highlighted. Exercise adherence will be recorded as a percentage of completed exercises during the first follow up (after the six-week intervention) for both groups. Exercise adherence will be taken into consideration when performing the pre-protocol analysis.

All enrolled patients will be encouraged to contact the principal investigator directly if experiencing problems related to their allocated group intervention. The principal investigator will then fill out a standardized form at these calls. Patients can use medicines and nutritional products as needed, prescribed by their physician. To avoid study-contamination, patients will be asked to adhere to the allocated rehabilitation intervention and not to seek alternative health-care services during the course of the study. Patients will be advised to contact their general practitioner or the principal investigator as needed.

The physiotherapy intervention will be given to Groups A and B for six weeks. The intervention will be provided for 60 minutes, five days each week. Both Group A and Group B will receive conventional treatment. Group A will receive mCIMT along with the conventional therapy, while Group B will receive the motor relearning program along with the conventional therapy. Treatment will be provided to both groups for six weeks.

*Modified constraint-induced movement therapy (mCIMT)*

Exercises will be given to participants that have a functional focus and will be under supervision. The affected lower extremity will be the focus of these exercises. Based on the desired movements, the therapist (principal investigator) recommended these exercises.

The 30-minute mCIMT approach will consist of the following movements: Transfer package (10 minutes per session), side stepping, ball kicking, stair climbing, and knee control on a step.

*Motor Relearning program (MRP)*

Participants receive task-specific guidance based on the MRP. This method will be applied for 30 minutes. The actions will be practiced in both sitting and standing and should target an individual’s particular deficits: supine to side-lying to sitting, looking up at ceiling (ensure that centre of body mass does not move back when head is tilted back), without moving one’s feet, turning to gaze over each other’s shoulders and scanning the surroundings for specific items, reaching motions in multiple directions while moving the head and trunk, scooting in bed, altering the base of support (standing with your feet together, in tandem, with one foot on a step, or on one leg), squatting to pick up an object and cross over stepping.

*Conventional therapy*

Conventional therapy includes: i) Passive and active assisted range of motion exercises for upper and lower extremities; ii) stretching exercises for flexor synergy component shown in
Table 1; iii) strengthening exercises with the help of THERABAND shown in
Table 2; iv) balance training including practicing reaching beyond arm’s length while sitting and standing; and v) walking training that includes challenge to dynamic balance (
*e.g.*, obstacle courses).

**Table 1. T1:** Stretching exercises for upper extremities, pelvic position and lower extremities.

Action of the muscles	Major muscles targeted	Procedure
• Scapular retraction or hyperextension, shoulder abduction, elbow flexion, forearm supination, wrist and finger flexion • Pelvic retraction • Hip flexion, abduction, external rotation, knee flexion, ankle dorsiflexion, inversion	• Pectoralis major, Pectoralis minor, Latissimus dorsi, Biceps brachii, brachioradialis, Supinator muscle, Flexor digitorum profundas, Flexor digitorum superficialis and Palmaris longus • Piriformis and Thoracolumbar fascia • Gluteus minimus, Gluteus medius, Psoas major, Iliacus sartarius, Rectus femoris, Hamstring, Tibialis anterior	Patient position: Supine and sitting Therapist position: Standing Mode of stretching: Manual stretching, slow repetition, continuous stretch Doses: 3 repetitions with 30 seconds hold

**Table 2. T2:** Strengthening exercises for upper extremities, pelvic position and lower extremities.

Action of the muscles	Major muscles targeted	Procedure
• Scapular retraction or hyperextension, shoulder abduction, elbow flexion, forearm supination, wrist and finger flexion • Pelvic retraction • Hip flexion, abduction, external rotation, knee flexion, ankle dorsiflexion, inversion.	• Rhomboid, Latissimus dorsi muscle, Deltoid, Triceps, Pronator teres, Extensor digitorium, Extensor digiti minimi. • Quadratus lumborum • Adductor mangus, Adductor longus, Adductor brevis, Gracillis, Gluteus maximus, Quadriceps, Gastrocnemius	Patient position: Supine and sitting Therapist position: Standing Progression: Strengthening exercises will be given with THERABAND (Yellow, Red and Green colour).

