### Sample size calculation

We estimated the sample size using a power analysis with 80% power and 5% Type 1 error for the main variables. The BBS score, in comparison to the difference in mean score pre and post treatment for mCIMT group from baseline to end visits. For the study, we used the previously determined effect size difference in percentage from the RCT.
^
22
^ Formula using mean difference:

$$n1=n2=2\frac{{\left(Z_{\alpha }+Z_{\beta }\right)}^{2}\sigma^{2}}{{\left(\delta \right)}^{2}}$$
Primary Variable (BBS)

Mean ± SD (Pre) result on BBS for mCIMT = 48.8 ± 4.7

Mean ± SD (Post) result on BBS for mCIMT = 52.5 ± 3.5

Difference = 3.7

Pooled std. dev. = (4.7 + 3.5)/2 = 4.1

$$\text{N1}=2^{*}\left[{\left(1.64+0.84\right)}^{2}{\left(4.1\right)}^{2}\right]/{\left(3.7\right)}^{2}=15$$

Considering 10% dropout = 2

Total samples required = 15 + 2 = 17 per group.

Total sample size required = 15

Notations:

$$Z_{\alpha }=\text{1.64 bat 5\% l.o.s. at both sides total 10\% type I error}$$

α=Type I error at 5%

$Z_{\beta }=0.84\;\left(1-\beta \right)=\text{Power at}\;80\%$

σ=std.dev=0.5pooledstd.dev

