### Data collection methods

Before group allocation, screening of the participants as per the inclusion and exclusion criteria will be carried out. This will be followed by baseline assessment of the outcome measures as mentioned. All participants will undergo the randomization process and are allocated into either group A or Group B. The intervention will be administered for an hour daily, five days per week for six weeks. The post intervention data for the outcomes will be recorded after the last intervention session day. The data will be compiled and analysed for studying the results. The study interventions will be administered by the principal investigator under the supervision of the guide throughout the duration of the study. The patients will be instructed and reminded of the sessions in advance through messages sent to their mobile phones so that adherence to the study is ensured. Furthermore, if the patient misses their sessions due to any reason, the standby days from the week will be utilized such that the patient receives a total of 30 sessions of intervention in the six week duration.

As per in the sample size calculation we have given a 10% dropout rate so that it does not interfere with the results of our study.

The data collection forms can be found as
*Extended data.*
^
24
^

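### The protocol ends study participation after a complication but also retains participants for follow-up; the two sentences conflict as written and should be reconciled for data collection

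*Protocol article*

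**What the plan says.** The relevant text is one short paragraph of the protocol article's Interventions section, under the subheading "Criteria for discontinuing allocated interventions for a given trial participant".

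- Its first sentence says that if a patient in either group develops any complication (deep venous thrombosis is the one example given), "their participation will be discontinued in the study".
- Its second sentence provides for appropriate care and outpatient rehabilitation.
- Its third sentence reads: "Study participants will be retained in the trial (unless they withdraw their consent) to enable follow-up data collection and to prevent missing data".

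Three other sections decide what follows from this:

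- **Outcome measures:** assessments are at baseline and six weeks only.
- **Statistical analysis:** "Full analysis set for the values of outcome variables will be analysed", and "missing data will be covered with imputation method by calculating the mean and median over the existing data".
- **Sample size calculation and Data collection methods:** the dropout allowance is 2 patients per group, and the article says of it that "we have given a 10% dropout rate so that it does not interfere with the results of our study".

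**The concern.** The first sentence ends participation in the study. The third keeps participants in the trial and allows one exception, withdrawn consent, which is not the same as a complication. Two members of staff could follow this paragraph in good faith and treat the week-6 visit in opposite ways.

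The choice matters because week 6 is the only assessment after baseline. A patient who leaves before it has no change score on either primary outcome, and the analysis would substitute the mean or median of the patients who stayed. If patients with complications tend to do worse on balance and gait, the substituted values are too favourable. The pre-post changes, which serve the first two objectives, would then be overstated. The comparison of mCIMT with MRP, the third objective, would be distorted as well if the number of complications or their effect differed between arms. The term *any complication* is not defined beyond the one example, and the trial is open-label with the principal investigator both assigning and delivering treatment, so equal handling in the two arms is not assured.

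**Working it through.** **1. The two rules side by side, for a patient who has a complication and does not withdraw consent**

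| Question | First sentence | Third sentence |
|---|---|---|
| Still in the study? | No | Yes |
| Week-6 BBS and DGI collected? | Not provided for | Yes |
| Value entering the analysis | Mean or median of observed patients | The patient's own value |

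The subheading speaks of the intervention and not of the study, which points to the third sentence as the intended rule. No sentence says that a complication stops treatment only.

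**2. The plan's own figures**

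Inputs from the Sample size calculation section: difference 3.7, SD 4.1, Z values 1.64 and 0.84.

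- n = 2 × (1.64 + 0.84)² × 4.1² / 3.7² = 2 × 6.1504 × 16.81 / 13.69 = 15.10, stated as 15.
- 10% of 15 = 1.5, rounded up to 2: "Considering 10% dropout = 2".
- 15 + 2 = 17, which agrees with "Total samples required = 15 + 2 = 17 per group".

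The figure of 17 per group reproduces, and the textual conflict does not depend on it. The allowance restores numbers, and so protects precision. It does nothing about bias when the reason for loss is related to the outcome.

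**3. Assumed illustration of the bias**

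The article gives neither a complication rate nor any outcome for such patients, so the following values are assumptions.

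- k = patients in one arm of 17 with no week-6 value after a complication.
- d = how much worse their unobserved BBS change is than the completers' mean change in that arm.
- The missing change is replaced by that arm's completers' mean. Leaving the patients out gives the same arm mean.

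If the completers' mean change is m, the true arm mean is [(17 − k)m + k(m − d)] / 17 = m − kd/17. The reported mean is m. The overstatement is therefore k × d / 17.

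| k | d = 3.7 | d = 5 | d = 8 | d = 10 |
|---|---|---|---|---|
| 1 | 0.22 | 0.29 | 0.47 | 0.59 |
| 2 | 0.44 | 0.59 | 0.94 | 1.18 |
| 3 | 0.65 | 0.88 | 1.41 | 1.76 |

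The range is 0.22 to 1.76 BBS points. At k = 2, the number the plan allows for dropout in one group, it is 0.44 to 1.18 points.

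**4. From one arm to the comparison**

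The bias in the difference between arms is (k_A × d_A − k_B × d_B) / 17. It is zero when the two products are equal, and reaches the tabulated values only when the loss falls in one arm. With equal loss, each arm's pre-post change is still overstated by k × d / 17.

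**The case against.** The strongest reply is that the paragraph largely explains itself. Its subheading is about stopping the intervention, its second sentence deals with care for the patients concerned, and its closing sentence on retention has little purpose there unless it covers those same patients. The Data management section also expects patients to be invited to a six-week examination and completion to be high. On that reading the only defect is a loose phrase. This stands to a large extent: it is the more natural reading, and it makes the correction easy. It does not make the correction unnecessary, because the first sentence names the study and the text nowhere limits the stop to treatment.

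Three further objections are sound and limit the point.

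- A reader might infer that the worst outcomes drop out of the data. The article does not support this. It reports no outcomes for patients with complications, and under the stated plan missing values are imputed rather than dropped. That such patients do worse is a reasonable inference, not a documented fact.
- A reader might take the 12% that results from k = 2 and d = 3.7 as an estimate of the effect. It is 2/17 restated: if the completers gain 3.7, the lost patients gain nothing, and the result is divided by 3.7, the gain cancels. Moreover, the article's 3.7 is a pre-post change in a single mCIMT group (48.8 to 52.5), although its formula uses it as the difference between groups.
- The weakness of filling gaps with a mean or median applies to missing data from any cause. It is a separate matter; here it only determines what happens to these patients' values.

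**Conclusion.** The two sentences conflict as written and should be reconciled. This is an inconsistency within one paragraph, with a likely benign intent and a real consequence if staff follow the first sentence literally. No stated number changes when it is resolved.

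The size is unknown because no complication rate is given. The illustrative overstatement of about 0.2 to 1.8 BBS points in one arm's mean change rests on four assumptions: 1 to 3 of 17 patients affected, a change 3.7 to 10 points worse than completers', imputation from the same arm's completers, and no week-6 assessment for those patients. It becomes bias between arms only to the extent that complications or their effects differ by arm.

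A reader might also conclude that the full analysis set is defeated. That goes too far: it would follow only if the retention sentence were disregarded. What can be said is that the present wording lets that happen.

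**What to change.** Reconcile the two sentences. For data collection and analysis only, state that:

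1. stopping the allocated intervention does not end participation in the trial;
2. the week-6 assessments already scheduled are sought for every randomised patient, unless consent is withdrawn or assessment is not possible;
3. these patients are analysed in the arm to which they were randomised.

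When treatment is stopped remains the clinicians' decision and is not addressed here.

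The cost is a sentence or two of protocol wording and no new visit. The article reports that the study has not begun, so no data are affected. Its Protocol amendments section says that further changes could not be carried out. This change resolves an internal conflict in line with the article's own retention aim and leaves the design as it is, so it can be recorded as a clarification.
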